# Design and baseline characteristics of the PerfectFit study: a multicenter cluster-randomized trial of a lifestyle intervention in employees with increased cardiovascular risk

**DOI:** 10.1186/s12889-015-2059-9

**Published:** 2015-07-28

**Keywords:** Motivational interviewing, Health risk assessment, Blended care, Work, Lifestyle change, Cardiovascular risk, General health, Cost-effectiveness, Decision aid

## Abstract

**Background:**

The prevalence of unhealthy lifestyles and preventable chronic diseases is high. They lead to disabilities and sickness absence, which might be reduced if health promotion measures were applied. Therefore, we developed the PerfectFit health promotion intervention with a “blended care”-approach, which consists of a web-based health risk assessment (HRA) including tailored and personalized advice, followed by motivational interviewing (MI). We hypothesize that adding MI to a web-based HRA leads to better health outcomes. The objective is to describe the design and baseline characteristics of the PerfectFit study, which is being conducted among employees with high cardiovascular risk in the military workforce, the police organization and an academic hospital.

**Methods:**

PerfectFit is a cluster randomized controlled trial, consisting of two arms. Based on cardiovascular risk profiling, done between 2012 and 2014, we included employees based on one or more risk factors and motivation to participate. One arm is the ‘limited’ health program (control) that consists of: (a) an HRA as a decision aid for lifestyle changes, including tailored and personalized advice, and pros and cons of the options, and (b) a newsletter every 3 months. The other arm is the ‘extensive’ program (intervention), which is additionally offered MI-sessions by trained occupational physicians, 4 face-to-face and 3 by telephone, and is offered more choices of health promotion activities in the HRA. During the follow-up period, participants choose the health promotion activities they personally prefer. After six and twelve months, outcomes will be assessed by online questionnaires. After twelve months the cardiovascular risk profiling will be repeated. The primary outcome is self-reported general health. Secondary outcomes are self-reported work ability, CVD-risk score, sickness absence, productivity loss at work, participation in health promotion activities, changes in lifestyle (smoking, alcohol consumption, physical activity, stress management) and body mass index. Furthermore, a process evaluation and an economic analysis will be performed.

**Discussion:**

Additional coaching using MI is expected to be a key factor for success of the web-based HRA in employees with increased cardiovascular risk. This “blended care”-approach may be an essential strategy for effective health promotion activities.

**Trial registration:**

Dutch Trial Register by registration number NTR4894, 14/11/2014.

## Introduction

### Background

Although life expectancy has significantly increased over the past decades in many countries worldwide, the prevalence of unhealthy lifestyles, preventable chronic diseases and disabilities is rising [1–3]. Combined with an ageing workforce, today’s sustainable employability and well-being of employees are under increasing pressure. Major risk factors for their well-being are adverse lifestyle habits, such as physical inactivity, unhealthy diet, smoking, alcohol and stress. These lifestyle behaviors are associated with chronic diseases, and among them, the most common are cardiovascular disease (CVD) and diabetes. These diseases not only produce high healthcare costs, but also high indirect costs to society due to productivity losses [4–6]. There is a clear need for health promotion interventions that are effective and feasible among employees.

Web-based health promotion interventions, such as a web-based health risk assessment (HRA), have been increasingly used [7–9]. They have the potential of a broad reach and, if appropriately designed and implemented, may promote health and well-being, reduce absenteeism, and increase work productivity [10–12], thus leading to a positive “return on investment” [13, 14]. A recent meta-analysis showed, however, that these intervention effects were found to decline after intervention completion. This report stated that there is a need for innovative techniques to help participants maintain their lifestyle changes [15]. A counselling technique that has shown promising results in changing and maintaining health behavior is Motivational Interviewing (MI) [16–23]. MI is a patient-centered coaching technique, and is based on four principles: showing empathy; addressing discrepancy between current behavior and an alternative lifestyle behavior; reinforcing the clients’ sense of self-efficacy; and respectfully dealing with the clients’ resistance to change [24]. Whereas an HRA informs a participant of their risks of CVD and the options for risk reduction, MI is used to help the participant evoke and strengthen intrinsic motivation for lifestyle changes by respecting individual preferences and autonomy. HRA complemented with MI could be considered a form of “blended care”. This type of care involves an internet approach and face-to-face care blended into one integrated treatment [25]. As of recently, the blended approach has been increasingly used to effectively influence changes in lifestyle behaviors [26] [27].

Based on a “blended care” approach, we developed and implemented an intervention study called PerfectFit. PerfectFit is aimed at employees who are 40 years or older, have high physical and mental work demands, and possess at least one risk factor for cardiovascular disease [28]. We hypothesized that adding MI to an HRA improves the effectiveness and sustainability in changing unhealthy lifestyles and reducing risk factors for chronic diseases [26]. The objective of this study was to find out whether adding MI to a web-based HRA leads to further improvement in the overall health status and in secondary outcomes such as participation in health activities, work ability, sickness absence and productivity at work, and lifestyle behavior. In this paper, a detailed description of the study design is presented, along with the baseline characteristics of participants. Short- and long-term results of the intervention, as well as a process and an economic evaluation will be presented in future papers.

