## Methods

### Study design

The PerfectFit study is a cluster randomized control trial [29] (cRCT) among employees of three organizations, aimed to compare two groups: a purely internet-based approach (*limited or control* intervention) and a group that is exposed to the internet-based approach supplemented with MI (“the blended approach”, *extensive* intervention). The internet approach consists of a web-based HRA (later addressed as “HRA“) with tailored and personalized advice for health behavior change as well as pros and cons of the options for change. In the extensive intervention, the HRA is supplemented with face-to-face care provided by an (in-house) occupational physician (OP) using MI. The elements of the intervention are based on existing modules, previously evaluated RCTs [22, 30–32] and a recent meta-analysis [33]. Measurements were done at baseline and will be repeated after 6 and after 12 months.

Participants were included between 2012 and 2014 after providing written informed consent. There were no risks associated with participating in PerfectFit. Confidentiality was guaranteed during the study for all participants, as no information about the cardiovascular risk profiling, the HRA, or the coaching was provided to others than stated in the Participant Information Form. Ethical approval was obtained from the Medical Ethical Committee of Erasmus MC Rotterdam (METC) by registration number MEC 2012–459. The trial was registered on November 14^th^ of 2014 at the Netherlands Trial Register by registration number NTR4894.

After trial commencement, three OPs withdrew because of other priorities in work or due to personal issues, resulting in the loss of one military cluster and less inclusions than expected. In order to achieve sufficient power, we obtained approval of the METC to include an additional organization (i.e., an academic hospital).

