#### Web-based HRA

The web-based HRA consists of a web-based electronic questionnaire, including questions on lifestyle, work, family history, medical history, and motivation to change, which takes 30 to 45 min to fill out. Based on the answers on these questions, as well as on the baseline anthropometric and blood measurements that are integrated in the online system, the web-based HRA generates tailored and personalized advice to the participant, which are presented as low-risk (green), intermediate-risk (orange), or high-risk (red) profiles. Personalized advice includes a suggestion of choice out of health promotion activities, based on the participant’s risk profile, preferences and motivational aspects, according to the transtheoretical model of health behavior change [39]. These optional choices can be selected from a list of activities that are “usual care” for each organization. Prior to the inclusion period, this list was constructed by the OPs and the research team, and it includes health promotion activities on lifestyle items (i.e. sports facilities, dietician, psychologist). This web-based HRA can be considered as a patient decision aid, since it meets the six qualifying criteria [40]. The flowchart of the intervention is shown in Fig. 2.

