### Limited (control) intervention

The limited health intervention program consists of the following elements:a web-based HRA (described above), including tailored and personalized advice for health behavior change, with a suggestion of choice out of three “usual care” health promotion activities for every identified risk factor. This is followed by usual care, according to Dutch OP guidelines [41].an electronic newsletter of approximately two pages, sent every three months. The newsletter includes general information on PerfectFit and on a healthy lifestyle.

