### Extensive intervention

In the extensive intervention group, the limited intervention program is extended with personalized MI sessions with an OP, together with additional tailoring based on motivational elements in the web-based HRA and an additional motivational paragraph in the newsletters.

MI is conducted in the form of individual coaching sessions run by trained OPs. Altogether, they include seven motivational coaching sessions: three face-to-face sessions (30–45 min per contact) and four telephone contacts (15–30 min per contact) [42]. The MI training for OPs was organized as a continuous medical education (CME) session and after successful completion of the training OPs received credits. The training was free of charge and it consisted of three full days of group training by a certified MI trainer with 3 follow-up coaching sessions of 4 hours each [43]. During the training, OPs became familiar with the basic principles of MI and they practiced techniques needed for conducting MI. The aim was to elicit long-term healthy behavior in the participants.

To assure and maintain a high level of quality of MI during the intervention period, we conducted two quality assurance activities [44]. First, after every three months, each OP was asked to audio record the first face-to-face consultation with a participant, using a voice recorder. Recorded sessions were transcribed verbatim and analyzed using the validated Motivational Interviewing Treatment Integrity code (MITI) for the presence of core elements of the MI technique, such as reflexivity, open-questioning, and empathy [45, 46]. Scorings were done by the first author and a co-investigator in this study, who are both experienced MI-coaches and familiar with the scoring technique. Within a month after the recordings, the OPs received feedback on the quality of their MI-techniques. Second, after every MI session with participants, OPs had to fill out a form related to the MI session with a participant, such as if it was a face-to-face or telephone session, the amount of time it took, and what stage of change the participant was in (5 stages, ranging from pre-contemplation to maintenance).

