The online advice within the HRA additionally includes tailoring based on motivational aspects such as intention to change and personal preferences, and it includes three more suggestions of choice for health promotion activities. In contrast to usual care, these additional suggestions of choice include e-health interventions, fitness centers with national coverage, and the use of an activity tracker (accelerometer). The accelerometer is offered for free and is primarily aimed at providing “biofeedback” to those participants who are physically inactive and who are motivated to improve their level of physical activity by using this small monitoring device during twelve consecutive weeks [47].

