## Discussion

The PerfectFit study aims to establish whether adding MI to a web-based HRA is a key-factor for improving effectiveness in changing unhealthy lifestyles and reducing risk factors for chronic diseases. MI is known to improve BMI, total blood cholesterol, systolic blood pressure, and blood alcohol concentration [73]. By adding MI, this superiority RCT combines the advantages of an online personalized and tailored approach with the advantages of a face-to-face approach, thus aiming to improve participation and sustained effectiveness of workplace health promotion programs [74].

Web-based healthcare (eHealth) is receiving growing attention since it can tailor interventions to target population characteristics (e.g., specific risk factors), thereby facilitating wider access and encouraging self-care, and possibly reducing health-care costs and improving efficacy [75]. However, a proven feature of eHealth is that its effect decreases after the intervention has been completed [15]. Our blended approach of adding MI to a web-based HRA is promising in several ways. First, we expect an increase of lifestyle changes, since previous research showed dose–response relationships between exposure to an intervention (number and duration of exposures) and behavior change outcomes [73, 76]. Second, it may lead to a higher sustainability of these lifestyle changes, since there is evidence that providing face-to-face counselling with a higher number of overall contacts was associated with greater short and long-term effectiveness [76]. MI has a large potential to fill the gap between the intention to change and the actual behavior change, commonly referred to as the intention-behavior gap [77]. This potential was previously demonstrated for lifestyle changes such as physical activity and a healthy diet [78–80]. MI is a unique tool for evoking and strengthening intrinsic motivation for a more sustainable change in lifestyle [13–19].

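### The stated objective is the effect of adding MI to the HRA, but the arms differ in four ways, so the trial can support a conclusion only about the extensive programme as a whole

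*Protocol article*

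**What the plan says.** Four places describe the contrast as HRA against HRA plus MI.

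- Background, objective: "The objective of this study was to find out whether adding MI to a web-based HRA leads to further improvement".
- Abstract, hypothesis: adding MI to the HRA is expected to give better health outcomes.
- Study design: one group has the internet approach only; the other is "a group that is exposed to the internet-based approach supplemented with MI".
- Discussion, opening: the study "aims to establish whether adding MI to a web-based HRA is a key-factor for improving effectiveness".

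The sections that describe the arms list more than MI.

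- Limited (control) intervention: the HRA offers, for each risk factor, a "suggestion of choice out of three “usual care” health promotion activities", followed by usual care and a quarterly newsletter.
- Extensive intervention: the limited programme plus seven MI sessions, "together with additional tailoring based on motivational elements in the web-based HRA and an additional motivational paragraph in the newsletters".
- On the activity menu of the extensive arm: "it includes three more suggestions of choice for health promotion activities". Unlike usual care, "these additional suggestions of choice include e-health interventions, fitness centers with national coverage, and the use of an activity tracker (accelerometer". The tracker is free and is meant mainly for inactive participants who want to become more active.

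The planned primary analysis (Statistical analyses) compares the extensive with the limited group. The three limitations in the Discussion are volunteer bias, attrition and lack of blinding. The additional components are not among them.

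**The concern.** The objective promises an answer about one component, while the design varies several components together. If the extensive arm does better, the wording leads straight to the conclusion that MI by occupational physicians made the difference. The same result could come from the wider choice of activities, the free tracker, the additional tailoring, or some combination. An employer deciding whether to train its physicians in MI would be relying on an attribution that the trial cannot make.

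Two outcomes are especially exposed. Participation is measured at 6 months by the number and type of activities chosen (Lifestyle section), and a longer menu can raise that count directly. Adherence to the physical activity guideline is also an outcome, and the tracker is offered for the purpose of raising activity.

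**Working it through.** No power or sample-size figure bears on this point, so the check compares the arms component by component and then asks what two arms can estimate.

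**Step 1: components by arm** (sections Limited (control) intervention and Extensive intervention)

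| Component | Limited | Extensive |
|---|---|---|
| MI sessions with an occupational physician | none | 7 |
| HRA tailoring on motivational elements | as in the common HRA | additional |
| Suggested activities | 3 | 3 + 3 = 6, including a free tracker |
| Newsletter | every three months | same, plus a motivational paragraph |

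The menu ratio is 6 / 3 = 2. The arms differ in four respects, of which MI is one. The tracker is one of the three extra suggestions and is not counted again.

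**Step 2: what the comparison estimates**

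Write M, T, A and N for the effects of MI, additional tailoring, additional activities and the newsletter paragraph. The expected difference between the arms is

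extensive − limited = M + T + A + N + all interactions among them.

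Four components that can each be present or absent give 2^4 = 16 combinations. The trial observes two: none present and all present. Two group means give one difference. The unknowns are 4 main effects and 16 − 1 − 4 = 11 interactions, 15 in total. One equation cannot identify M. The effects may also have opposite signs or depend on one another, so M is not even bounded between zero and the observed difference.

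**Step 3: are the extras part of MI by the document's own definition?**

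No. The Background defines MI as a coaching technique, and the Extensive intervention section says it is delivered as individual sessions by trained physicians. The menu, the tracker and the online tailoring belong to the HRA, which Study design presents as common to both arms.

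**Step 4: does any planned analysis separate the components?**

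The article describes none. The process evaluation records the amount, duration, timing and quality of MI sessions. Those data exist only in the extensive arm, so relating them to outcome is a non-randomised comparison that may reflect motivation.

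**Step 5: what does the control HRA contain?**

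The Web-based HRA section, which describes the tool for both arms, says that advice rests on "preferences and motivational aspects, according to the transtheoretical model of health behavior change". The Extensive intervention section then presents tailoring on motivation and preferences as something added. The text does not say how much of it the control arm receives.

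**The case against.** The strongest reply is that testing a multicomponent programme in two arms is a legitimate pragmatic design, and that the components are openly described. The Abstract mentions the wider choice of activities, the arm descriptions itemise the rest, the primary analysis is labelled extensive against limited, and the Discussion closes by asking about the blended care approach. MI is also much the most intensive element: seven individual sessions against optional suggestions. The tracker is aimed mainly at inactive participants, and Table 2 reports lack of physical activity in 96 (36.9%) of the extensive arm. All of this stands. It shows that the package comparison is sound and that MI may well be the main driver. It does not make MI's share estimable, and disclosing the components does not change an objective that names MI alone.

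Several stronger readings are tempting, and the documents do not support them:

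- A reader might count the tracker as a fifth difference. It is one of the three extra suggestions.
- A reader might infer that the arms receive different newsletters. The difference is one added paragraph.
- A reader might infer that the economic evaluation is wrong. The Statistical analyses and Economic evaluation sections cost the extensive against the limited programme, with the web portal as well as MI training among the direct costs. Only a Discussion remark ties its result loosely to the investment in MI training.
- A reader might see a flat contradiction about the control HRA. Basic tailoring for both arms with more in one arm is a coherent reading, so the text is unclear rather than contradictory.

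**Conclusion.** The point holds as a mismatch between the stated objective and the contrast that the design delivers. MI is one of four simultaneous differences between two arms, so its own effect is not identifiable. The randomised comparison of the whole extensive programme with the whole limited programme is unaffected. No numerical share can be attached to MI; a statement such as anywhere from none to all of the effect would not be a calculation either, because of possible interactions and opposing effects.

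The consequence is greatest for participation in health activities and for physical activity. For self-rated general health, the primary outcome, the same limit applies, though the route from the extra components is less direct. The verdict rests on the arms being delivered as described and on no further arm or contrast existing outside the article. No results are reported in it, so the wrong attribution is a risk that the wording creates and has not yet occurred in a results paper.

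**What to change.** 1. Restate the objective, hypothesis and planned conclusion as the effect of the extensive (blended) programme compared with the limited programme, in the Abstract, Background, Study design and Discussion.
2. Remove, as conclusions of this trial, the phrasing about whether adding MI improves outcomes and about MI being a key factor. It can remain as rationale.
3. Add to the limitations that MI cannot be separated from the additional tailoring, the wider menu with the tracker, and the newsletter paragraph, and name participation and physical activity as the outcomes most affected.
4. State in the Web-based HRA, Limited and Extensive sections which motivational tailoring both arms receive and which only the extensive arm receives.
5. Label analyses of MI-session data, and any data on tracker use, as exploratory.
6. Leave the economic comparison as planned, but do not credit its result to MI training alone.

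The cost is rewording and a narrower claim. The Background leaves the effect results to later papers, so the change can be made there before they are reported.
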